## Abstract

Systemic lupus erythematosus (SLE) has a spectrum of phenotypes. Its management should target remission or low disease activity, prevention of relapses and organ damage, minimisation of drug-related harms, and optimisation of health-related quality of life. Advances in our understanding of the disease pathophysiology have expanded the treatment armamentarium with targeted biologics that demonstrate superiority over conventional drugs in controlling activity, reducing flares and glucocorticoid exposure, and improving patient-related outcomes. In view of this, there is a critical need for real-world evidence providing insight into the spectrum of activity, the treatment landscape, and unmet needs among SLE patients. Such information can support regulatory and reimbursement decision-making. The primary objective of the NYMERIA multicentre study is to generate real-world evidence on the activity state of SLE patients treated in routine care settings in Greece. The overarching aim is to capture the disease burden based on both clinical aspects and the patient perspective.

## INTRODUCTION

Systemic lupus erythematosus (SLE) is a chronic multi-system autoimmune disease, with a mosaic of phenotypes spanning from mild musculoskeletal and mucocutaneous manifestations to life-threatening organ involvement. While SLE frequency shows worldwide variability attributed to genetic, environmental exposure, diagnostic and methodological differences,^1^ prevalence estimates in Greece range between 39.5 to 123.4 per 100,000 adults.^2–4^

Despite advances in the disease management, significant challenges still remain.^5^ Thus, lupus patients tend to follow a fluctuating pattern of disease activity, with periods of remission alternating with flares.^6^ Moreover, a sizeable number of individuals may experience periods with persistently active, mild-to-moderate activity. Active disease, typically requiring extended intake of glucocorticoids, carries an increased risk for adverse consequences especially accrual of irreversible organ damage, which is a major driver for excessive morbidity and mortality. Furthermore, SLE patients suffer from impaired health-related quality of life (HRQoL), comparable to their counterparts with diabetes mellitus, myocardial infarction and other chronic disorders.^7^ In fact, HRQoL in SLE shows only partial correlation with disease activity^8^; rather, it may be affected by other factors including long-standing complications (i.e., damage) and fatigue. Indeed, the latter parameter is often under-treated by the physicians due to its subjective nature and multidimensional causes despite the fact it can impact on patient’s work ability and productivity, thus resulting in increased rates of unemployment and absenteeism.^9^

It is widely recognised that SLE treatment should aim at sufficient control of disease activity under no or minimal dose of glucocorticoids.^10^ Accumulating evidence supports that sustained attainment of either remission or low disease activity – both states requiring a maintenance dose of oral glucocorticoids ≤5 and ≤7.5 mg/day of prednisone equivalent – are linked to slowing or prevention of SLE exacerbations and organ damage.^11^ The favourable effects of achieving these targets may extent to other relevant outcomes including improvements in HRQoL.^12,13^ The importance of ‘treating-to-target’ strategy has been appreciated in the 2019^14,15^ and 2023^16^ update of the EULAR (European Alliance of Associations for Rheumatology) recommendations for the management of SLE. In this context, novel biological agents approved for lupus including belimumab and anifrolumab, have demonstrated superiority over conventional drugs in achieving low disease activity/remission,^17–19^ reducing flares,^20,21^ and cumulative exposure to glucocorticoids22,23 while conferring beneficial effect on patient-reported outcomes.^24,25^ To this end, EULAR has emphasised the timely initiation of these biologics in SLE patients who despite treatment with antimalarials (with or without glucocorticoids and/or immunosuppressants), they do not achieve sufficient disease control or require >5 mg/day of prednisone equivalent.^16^

In view of the above and in light of the new targeted therapies becoming available, there is a need for contemporary, real-world evidence spanning different geographical regions and settings. This data could offer valuable insights into the spectrum and burden of disease activity, the prevailing treatment landscape, and unmet needs among individuals with SLE. Also, to aid towards a holistic patient-centred approach to the disease while also, serving as valuable input for health technology assessment submissions and supporting regulatory and reimbursement decision-making for the aforementioned awaited new technologies.^26,27^ Here, we outline the design and methodology of a multicentre, cross-sectional study employing both chart-based assessment and single visit evaluation in 200 Greek SLE patients managed under real-life condition.

## METHODOLOGY

### Overview of the study design

This is a single-country, multicentre, cross-sectional, and retrospective chart review study with a single-visit data collection schedule, which aims at including a representative sample of adult outpatients with SLE treated by rheumatology specialists in routine clinical care settings in Greece. The study will be carried out by 12 sites comprising hospital clinics experienced in SLE care in different parts of the country. No changes to the standard of care will be required and every part of patient care and clinical management will follow local medical practices and relevant national regulations, and will be decided by the participating physicians.

The conduct of this study will adhere to the applicable national regulatory requirements governing the conduct of such type of clinical research. Moreover, the study has been designed and will be conducted and reported in accordance with the ethical principles laid down in the Declaration of Helsinki, the Guidelines for Good Pharmacoepidemiology Practice (GPP) of the International Society for Pharmacoepidemiology, the STROBE (Strengthening the Reporting of Observational Studies in Epidemiology) guidelines where applicable, the EU General Data Protection Regulation (GDPR), and the local rules and regulations. The study will be completed in a single patient visit taking place within the normal clinical practice setting, and study-related information will be collected through routine clinical assessments that will be performed at the study visit, patient self-report and self-administered patient-reported outcomes (PROs), as well as through retrospective medical chart review. A representative of the Hellenic Federation of Associations of Patients, Parents, Guardians and Friends of Children with Rheumatic Diseases, “REUMAZIN”, was requested by the study team to provide feedback on suggested PROs relevant to SLE patients.

### Data sources and instruments

Data will be collected using a specific web-based data capture (WBDC) system (electronic Case Report Form [eCRF]) produced by the designated Clinical Research Organisation (CRO), which will adhere to all applicable data protection regulations and requirements. Data collection will be carried out by the participating physicians as part of standard clinical practice during routine assessments conducted at the single study visit. Additionally, patients will contribute data through the use of Patient-Reported Outcomes (PROs) and self-reports, where applicable. No further clinical, laboratory and imaging assessments are required apart from those performed as per the treating physician’s routine medical practice.

Patient source data pertaining to medical and SLE-related history, flare history, hospital-based HCRU over the past 12 months, results of laboratory tests of interest, and SLE management practices will be abstracted from patients’ medicals records and patient self-report. Current and past medications administered for SLE will be recorded and presented in terms of pharmacological categories (i.e., antimalarials, glucocorticoids [GCs], immunosuppressive, biological agents, non-steroidal anti-inflammatory drugs, other) and drug classes except for GCs, in which case active substance, route of administration and dosage (for the current GCs as well as for those received over the past 12 months before enrolment) will be also collected to allow for conversion to prednisone equivalents. Recorded terms of medical history and comorbidities will be coded using the Medical Dictionary for Regulatory Activities (MedDRA) terminology (the last updated version available at the onset of medical coding) in preferred term and system organ class.

SLE clinical instruments will include: a) the clinical SLEDAI-2K (cSLEDAI-2K),^28^ in which the immunological items (anti-dsDNA and complement levels) are excluded, thus facilitating the evaluation of disease activity in daily clinical practice when results from serological tests are often lacking; b) clinical SLEDAI-2KG, which represents a modification of the SLEDAI-2K introduced to describe disease activity while accounting for GC dose category^29^; c) Physician Global Assessment (PhGA), which is a responsive instrument that reflects the clinician’s judgment of overall SLE disease activity on a scale between 0 (no), 1 (mild), 2 (moderate) and 3 (most severe disease activity/severity)^30^; and d) the SLICC/ACR Damage Index (SDI), which has been extensively validated to capture irreversible dysfunction/damage in 12 organ/systems accrued as a consequence of either disease activity, received treatments or comorbidities.^31^

The following PROs will be collected via self-administered paper questionnaires completed by the patients themselves at study enrolment: a) LupusPRO, which is a validated survey tool developed for lupus patients to measure the impact of the disease and its treatment both on their health-related (HRQoL) and non-health-related quality of life (N-HRQoL)^32^; b) EQ-5D-5L,^33^ a generic HRQoL instrument that produces country-specific value sets therefore facilitating the calculation of quality-adjusted life years that are used to inform economic evaluations of health care; c) Work Productivity and Activity Impairment (WPAI):Lupus,^34^ which is a validated self-administered Lupus-specific version of the WPAI questionnaire that records impairment in work and general activities due to SLE over a 7-day period; and d) Fatigue Severity Scale (FSS), a self-administered 9-item scale measuring the severity of fatigue and its effect on patients’ daily functioning.^35^ Self-administered Greek versions of the aforementioned PROs will be provided to the enrolled patients. The questionnaires will be distributed prior to the patient undergoing any additional procedures or clinical examinations during the study visit. This will occur before the patient receives information about the current state of their disease or any adjustments to the therapeutic strategy. This timing is deliberate to ensure that interactions with healthcare professionals do not unduly impact the patient’s responses.

### Study population, inclusion and exclusion criteria

A total of 200 patients eligible for participation in the study according to the inclusion and exclusion criteria outlined below will be recruited over a 12-month period. Each participating site is expected to recruit between 10 and 30 patients. Patient selection will be based on consecutive sampling method, i.e., all consecutive eligible and consenting patients are expected to be included in the study. To mitigate potential selection bias, physicians will be requested to consecutively enrol the first eligible patients (based on the site-specific target) attending their clinic/office over the pre-specified study recruitment period.

For inclusion in the study, patients should fulfil the following criteria: i) male or female adult outpatients aged between 18 and 65 years old (inclusive); ii) documented, physician-based diagnosis of SLE ascertained by the formal classification criteria for SLE (1982/1997 ACR and/or 2012 SLICC and/or 2019 EULAR/ACR criteria); iii) disease duration of at least 12 months; iv) information available for scoring the cSLEDAI-2K over the 30 days prior to enrolment, or for patients whose physicians plan to perform such measurements at the study visit as part of their routine practice, regardless of their decision to include the patient in the current study.; v) accurate and complete medical records for data abstraction to meet the objectives of the study; vi) patients willing and able to read, understand and complete the provided patient questionnaires; vii) patients must provide a written informed consent prior to inclusion in the study.

Patients will be excluded if any of the following criteria are met: i) coexisting systemic rheumatic/autoimmune disease (including, among other others, rheumatoid arthritis, multiple sclerosis, systemic sclerosis); b) active malignancy diagnosed prior to SLE diagnosis; c) ongoing pregnancy; d) treatment with any non-approved drug/device/intervention or patients who have received any investigational product within 1 month or 5 half-lives of this product (whichever is longer) at the time of enrolment; e) patients who have already been enrolled in this study or in a study of the same design which the physician has good reasons to believe that it is this study (to exclude enrolment of the same patient by two different sites).

### Study outcomes and statistical analysis

The primary and secondary outcomes of the study are outlined in **Table 1**. Statistical analysis and generation of tables and patient data listings will be performed using the latest version of SAS^®^ software available at analysis onset. Statistical analysis will descriptive, not focusing to confirm or reject any pre-defined hypotheses. Continuous variables will be summarised using descriptive statistical measures [number of patients with available observations (npt), number of missing observations (nmiss), mean, SD, median, 25th and 75th percentiles, minimum (min) and maximum (max)] and categorical variables will be displayed using frequency tables including the respective 95% Clopper-Pearson Confidence Intervals (CIs) (where indicated), in the overall study population and the relevant defined subgroups by disease activity state. The normality of distribution of continuous variables will be examined using the Shapiro-Wilk test.

**Table 1. T1a:** Primary and secondary objectives of the NYMERIA observational study.

**Primary Outcomes**		
[1]	-	Proportion of patients classified as having at least moderate clinical disease activity, defined by a cSLEDAI-2K score ≥6.
	-	Proportion of patients classified as having at least moderate clinical disease activity, defined by a cSLEDAI-2KG score ≥6.
	-	Proportion of patients classified as having at least moderate clinical disease activity, defined by a PhGA score >1.
[2]	-	Frequencies of different clinical disease activity states (i.e., no activity, mild, moderate, high, and very high activity) using the cSLEDAI-2K, the cSLEDAI-2KG, and the PhGA score, respectively.
	-	Reclassification rate and concordance (kappa coefficient) between the different indices (i.e., cSLEDAI-2K and cSLEDAI-2KG; cSLEDAI-2K and PhGA; and cSLEDAI-2KG and PhGA) in terms of patient distribution in the “inactive/mild” and the “at least moderate” disease activity state.
[3]	-	Proportion of patients in clinical remission (as per the 2021 DORIS definition) defined as cSLEDAI-2K=0 and PhGA<0.5; the patient may be on AMs, low dose GCs (prednisolone equivalent<5 mg/day), and/or stable IS including biologics.

**Table T1b:** Secondary Outcomes^1^

[1]	-	Patient’s demographic and clinical characteristics, overall and by disease activity state.
[2]	-	LupusPRO overall score, total HRQoL and N-HRQoL constructs’ scores, and individual domain and item scores at the study visit.
	-	EQ-5D-5L utility index score and EQ-Visual Analogue Scale (VAS) score at the study visit.
	-	Proportion of patients with reported problems for each level on each dimension of the EQ-5D and proportion of patients with ‘no problems’ (i.e., level 1) and ‘with problems’ (i.e., level 2 to 5).
[3]	-	WPAI:RS domain scores referring to absenteeism, presenteeism, and work productivity loss, among the study population who are employed at the study visit.
	-	WPAI:RS domain score referring to activity impairment among all patients.
[4]	-	FSS total and item scores.
	-	Proportion of patients with an FSS total score ≥36 indicating the presence of clinically significant fatigue.
[5]	-	Total SDI score.
	-	Proportions of patients with and without organ damage (i.e., with SDI score ≥1 and 0, respectively), and frequencies of the different SDI states (SDI score: 0, 1, 2, 3, 4 and ≥5).
	-	Frequency of damage in the different organ systems/domains and items of the SDI.
[6]	-	Number of swollen (SJC) and of tender joints (TJC) based on 28-joint counts, and total number of affected joints (swollen and/or tender).
	-	Moderate to severe joint disease activity (active joint count of ≥8 tender and/or swollen joints).
	-	Swollen to tender joint ratio (STR [SJC/TJC]) and frequencies of low (STR <0.5), moderate (0.5 ≤ STR ≤ 1.0), and high (STR >1.0) joint disease activity.
	-	Percentage of body surface area (BSA) affected by SLE.
	-	Moderate to severe skin disease as reflected by a BSA affected by SLE ≥10%.
[7]	-	Frequencies of current pharmacologic treatments by type/pharmacological category [monotherapy, combination regimen; AMs, GCs, IS, biological agents, NSAIDs, other], drug class, treatment duration, and number of dose intensifications since the start of current treatment including reason for intensification.
	-	Types and frequencies of past (before the start of current treatment) pharmacologic treatment modalities by pharmacological category and drug class.
[8]	-	Correlation coefficient and association (through linear regression analysis) of the SLEDAI-2K score, SLEDAI-2KG score, and PhGA score (as continuous variables), each with the following: SDI score; LupusPRO HRQoL total and individual domain scores; LupusPRO N-HRQoL total and individual domain scores; WPAI overall work productivity loss; WPAI activity impairment score; FSS score.
[9]	-	Association of patient, disease and treatment characteristics with the presence of at least moderate disease activity determined using the cSLEDAI-2K.
	-	Association of patient, disease and treatment characteristics with the presence of at least moderate disease activity determined using the cSLEDAI-2KG.

1 The numbering of the outcomes follows the numbering of the corresponding objectives. All outcomes will be assessed in the overall study population and in the subpopulations 1A / 1B & 2A / 2B, except for #8 and #9.

The concordance between the different indices will be determined using the kappa coefficient and the percentage of agreement. The correlation and the association of the cSLEDAI-2K, SLEDAI-2KG, and PhGA scores with the SDI and selected PRO scores will be examined using the Pearson’s or Spearman’s correlation coefficient and linear regression models, respectively. Logistic regression models, using both the univariable and multivariable approach, will also be used to evaluate the association of patient, disease and treatment characteristics with the presence of at least moderate disease activity, as determined by cSLEDAI-2K and by cSLEDAI-2KG, in the overall study population. In the context of the exploratory objectives, the annual rate of flares, hospitalisations and ED visits with the respective 95% Poisson confidence intervals (CIs) will be estimated. Missing data will be reported. No imputation methods will be performed in regards to missing data with the exception of partial dates which will be defined in more detail in the SAP. With regards to the scoring and handling rules of any missing PRO items, the relevant scoring instructions, where available, will be followed. All statistical tests will be two-sided and performed at a 0.05 significance level.

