### Sample size

In view of the exploratory/descriptive nature of the study and based on practical considerations, a sample size of 200 eligible patients is considered both feasible and sufficient for estimating the primary outcome measures. This number offers a maximum margin of error of 7.1% (with 95% CI using the Clopper-Pearson exact method ranging between 42.9% and 57.1%) for the estimation of a percentage of 50%, which represents a scientifically acceptable level of precision. Also, this sample size ensures that for any of the defined study subpopulations representing at least 50% of the overall population, frequency estimates of interest may be determined with a margin of error not exceeding 10.2%, therefore ensuring sufficient precision to draw meaningful conclusions.

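### Primary outcome [3] sets the glucocorticoid limit for remission at <5 mg/day and the Introduction gives ≤5 mg/day, so otherwise eligible patients on exactly 5 mg/day are in or out depending on the text applied

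*Protocol article*

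**What the plan says.** Table 1 of the protocol article, primary outcome [3], reads "Proportion of patients in clinical remission (as per the 2021 DORIS definition) defined as cSLEDAI-2K=0 and PhGA<0.5". It then lists the treatments a patient in remission may be taking, among them "low dose GCs (prednisolone equivalent<5 mg/day), and/or stable IS including biologics". A dose of exactly 5 mg/day therefore falls outside remission.

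The Introduction discusses the benefits of "sustained attainment of either remission or low disease activity" and describes these as "both states requiring a maintenance dose of oral glucocorticoids ≤5 and ≤7.5 mg/day of prednisone equivalent". Taken in order, this is ≤5 mg/day for remission and ≤7.5 mg/day for low disease activity, so exactly 5 mg/day falls inside remission.

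The unit also differs in name: prednisolone equivalent in Table 1, prednisone equivalent in the Introduction. Under Data sources and instruments, glucocorticoid substance, route and dosage "will be also collected to allow for conversion to prednisone equivalents".

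On precision, the Sample size section states that "a sample size of 200 eligible patients is considered both feasible and sufficient for estimating the primary outcome measures". It gives a maximum margin of error of 7.1% at a percentage of 50%.

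**The concern.** A threshold inside a primary outcome is stated one way where the outcome is defined and another way where the same clinical state is introduced. The conflict is confined to one dose, but that dose is a round number at which patients may well cluster.

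The study is descriptive and tests no hypothesis, so the estimated proportion is itself the result. Moving the boundary shifts that proportion in one direction. A confidence interval describes sampling error and does not cover such a shift. The article also says that its evidence should support regulatory and reimbursement decisions, so a reader needs to know which remission rule produced the figure.

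**Working it through.** **1. The two rules side by side**

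| Patient with cSLEDAI-2K=0 and PhGA<0.5 | Table 1 (<5) | Introduction (≤5) |
|---|---|---|
| Dose below 5 mg/day, or none | remission | remission |
| Dose exactly 5 mg/day | not remission | remission |
| Dose above 5 mg/day | not remission | not remission |

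Only the middle row changes. A patient on exactly 5 mg/day who fails either activity criterion is not in remission under both rules. Primary outcomes [1] and [2] do not use this cut-off.

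**2. Direction.** Everyone counted under <5 is also counted under ≤5, so the strict rule can give only an equal or lower proportion.

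**3. The plan's own precision.** Exact Clopper-Pearson limits for 100/200 are 42.87% and 57.13%, a margin of 7.1 points. For 50/100 they are 39.83% and 60.17%, a margin of 10.2 points. Both stated margins reproduce, and neither depends on the cut-off.

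**4. Size of the shift.** Let p be the proportion in remission under ≤5, and q the share of those patients who take exactly 5 mg/day. Then shift = p × q. With n = 200, each affected patient moves the estimate by 1/200 = 0.5 points. The article gives neither p nor q, so the values below are assumptions. Shift in percentage points:

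| | q = 5% | q = 10% | q = 20% | q = 30% |
|---|---|---|---|---|
| p = 20% | 1.0 | 2.0 | 4.0 | 6.0 |
| p = 30% | 1.5 | 3.0 | 6.0 | 9.0 |
| p = 40% | 2.0 | 4.0 | 8.0 | 12.0 |

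Worked case, p = 30% and q = 20%: 60/200 = 30.0% (95% CI 23.7% to 36.9%) under ≤5. Removing 60 × 0.20 = 12 patients leaves 48/200 = 24.0% (18.3% to 30.5%) under <5.

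Three of the twelve cells exceed 7.1 points. The shift passes that margin once 15 patients are affected (15/200 = 7.5 points).

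**The case against.** The strongest reply is that Table 1 is the only operative definition. It is complete, and a programmer would not take a cut-off from the Introduction, which is background text, does not name DORIS and defines no endpoint. The full dose is recorded, so either rule can be applied later, and a SAP is promised before database lock. Much of this stands: no data are lost and the repair is small. It does not remove the conflict. The article fixes the threshold explicitly in a primary outcome and describes remission differently elsewhere, so this is not detail left to the SAP.

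A character lost in text extraction cannot be excluded. It is not the obvious explanation, because the same table prints ≥6, ≥36 and 0.5 ≤ STR ≤ 1.0 correctly.

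Four stronger readings are tempting and unsupported:

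- **All patients on exactly 5 mg/day are affected.** Only those who also meet both activity criteria change class.
- **Table 1 is the text in error.** The cited definition is not at hand. The article shows that the cut-offs differ, not which is right, so the DORIS label cannot be called wrong and the Introduction may be the text to correct.
- **The Introduction states the remission cut-off twice.** Its later wording, "they do not achieve sufficient disease control or require >5 mg/day of prednisone equivalent", concerns when biologics should be started. It does not define remission.
- **The size can be derived from the earlier Greek cohort in the Discussion** (66.0% on glucocorticoids, 22.0% above 7.5 mg/day). If the 22.0% is a share of all patients, 66 − 22 = 44% take a dose up to 7.5 mg/day; if it is a share of users, 66 − 0.22 × 66 = 51.5% do. Neither figure shows how many take exactly 5 mg/day. The article also says that this cohort was selected towards active disease, and contrasts the present study with it.

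**Conclusion.** The point holds as an unreconciled boundary in one primary outcome. For patients with cSLEDAI-2K=0, PhGA<0.5 and exactly 5 mg/day, remission status depends on which text is applied, and the strict version can only lower the proportion.

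That much rests on the wording alone, with one reading step: the Introduction's two doses are matched in order to its two states. The size is not documented. The range of 1 to 12 points follows from the assumed p and q, so the effect may be trivial or may exceed the stated margin. The sample-size statement is unaffected.

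**What to change.** Before the outcome is programmed:

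1. Check the Introduction and primary outcome [3] against the cited definition and reconcile them.
2. State one classification boundary, saying explicitly how exactly 5 mg/day is handled, in Table 1 and in the derivation specification.
3. Use one unit name throughout, prednisone or prednisolone equivalent.
4. Tabulate the patients on exactly 5 mg/day who meet both activity criteria, so that the proportion can be read under either rule.

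The cost is a symbol and a unit name in the text, one line in the derivation and one extra table row. No new data are needed, because glucocorticoid dosage is already collected. This is a matter of classification for analysis and implies nothing about treatment.

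### Secondary outcome [7] gives dose intensifications only as a count over an open-ended, patient-specific window, so subpopulation figures mix frequency of intensification with time on treatment

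*Protocol article*

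**What the plan says.** In Table 1 of the protocol article, secondary outcome [7] describes current pharmacological treatment. Among its items are treatment duration and the "number of dose intensifications since the start of current treatment including reason for intensification". Duration and count stand next to each other, but neither is stated as the denominator or offset of the other.

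Footnote 1 to Table 1 sets the reporting groups: "All outcomes will be assessed in the overall study population and in the subpopulations 1A / 1B & 2A / 2B, except for #8 and #9". Outcome [7] is not among the exceptions. The article does not define these four labels, but the section on study outcomes and statistical analysis says summaries are given "in the overall study population and the relevant defined subgroups by disease activity state". I read the labels as referring to those subgroups.

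The same section calls the analysis descriptive, "not focusing to confirm or reject any pre-defined hypotheses". For other recurrent events it plans a rate under the exploratory objectives: "the annual rate of flares, hospitalisations and ED visits with the respective 95% Poisson confidence intervals (CIs) will be estimated". Dose intensifications are not named there.

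The eligibility criteria require "disease duration of at least 12 months" and set no maximum. They place no limit, lower or upper, on time on current treatment.

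**The concern.** A count of recurrent events can be read as a frequency only if everyone was observed for the same length of time, or if the count is divided by that time. Here the window opens when the current treatment started and closes at the study visit, so it may be short for one patient and many years long for another.

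Set side by side for the activity subgroups, the counts invite the reader to judge which group is intensified more often. If the groups differ in time on current treatment, the counts cannot answer that. They may show a difference where the rates are equal, or hide one where the rates differ. The article presents the study as evidence on the treatment landscape and unmet needs, and as input to reimbursement decisions. How often treatment is stepped up is part of that picture.

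**Working it through.** **The plan's own figures.** The documents give no expected count, rate or duration for dose intensifications, so there is no figure on this point to reproduce. The only precision figures are in the sample size section. Exact Clopper-Pearson limits at 50% reproduce them:

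- N = 200: 42.87% to 57.13%, half-width 7.13% (stated 7.1%).
- n = 100: 39.83% to 60.17%, half-width 10.17% (stated 10.2%).

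They concern proportions and do not bear on the count.

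**Formula.** Let group g have intensification rate r_g per patient-year and mean time on current treatment d_g. With a rate that is constant over time:

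- mean count in group g = r_g × d_g
- ratio of mean counts = (r_1 / r_0) × (d_1 / d_0)

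The count ratio equals the rate ratio only when d_1 = d_0.

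**Range.** The duration ratio drives the distortion, so it is the input to vary. All values below are assumptions.

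| Duration ratio d_1/d_0 | Count ratio if rate ratio = 1 | Count ratio if rate ratio = 2 |
|---|---|---|
| 0.25 | 0.25 | 0.5 |
| 0.5 | 0.5 | 1 |
| 1 | 1 | 2 |
| 2 | 2 | 4 |
| 4 | 4 | 8 |

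**Three worked cases (assumed rates and durations).**

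1. Equal rates, unequal durations: 0.5 per year over 1 year against 0.5 per year over 4 years. Mean counts are 0.5 × 1 = 0.5 and 0.5 × 4 = 2.0. The count ratio is 0.25; the rate ratio is 1.0.
2. Unequal rates, offsetting durations: 1.0 per year over 2 years against 0.5 per year over 4 years. Mean counts are 1.0 × 2 = 2.0 and 0.5 × 4 = 2.0. The count ratio is 1.0; the rate ratio is 2.0.
3. Equal durations: 1.0 against 0.5 per year, both over 4 years. Mean counts are 4.0 and 2.0. Count ratio and rate ratio are both 2.0, so nothing is distorted.

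**Can the reader recover the rate from what is listed?** Total events divided by total person-time equals mean count divided by mean duration, provided both means cover the same patients and the same treatment. If the tables happen to show that, a crude rate can be worked out, but without a confidence interval. It cannot be worked out from medians, or if duration is tabulated by drug class and the count by patient. The article does not commit to a layout.

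**The case against.** The strongest case on the other side has five parts.

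- **No comparison is planned.** The analysis is descriptive, and none of the listed agreement, correlation or regression analyses involves dose intensifications. This stands: the point concerns how the figures will be read, not an invalid test.
- **Exposure is listed in the same outcome.** This is true and softens the point. Separate group summaries of count and duration still do not replace a rate with an interval.
- **The direction of any bias is undocumented.** A reader might infer that active patients have shorter windows because their treatment was changed recently, so that their counts would look falsely low. The documents do not support this. The discussion mentions change or intensification of therapy only as the way an earlier Greek study ascertained active disease. A dose intensification is also counted within the current treatment, so it does not by itself restart the window.
- **The annual rates are a weak precedent.** They belong to exploratory objectives, and hospital-based resource use is collected over the past 12 months, where an annual rate is the natural summary. They show that the study is prepared to report rates; they do not make the count inconsistent with the plan.
- **A rate has its own assumption, and the SAP may already add one.** If intensifications cluster soon after a treatment starts, the rate too depends on duration. With combination regimens the denominator must be specified. Both are reasons to define the rate with care and to keep the count beside it. The SAP is not shown and may contain a rate; the outcome as published is a count.

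**Conclusion.** The point holds as a minor one. As defined, the count mixes frequency of intensification with time on treatment. If time on treatment differs between the subpopulations, the side-by-side counts will mislead by exactly the duration ratio, under a constant rate. No size can be given for this study, because the documents contain neither rates nor durations. Any particular multiple, such as fourfold, only restates the durations assumed.

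Two stronger readings should be avoided. The count does not reflect duration instead of frequency: it is the product of both and is undistorted when durations are equal. Nor can it be said that the message on unmet need will be reversed: that requires a duration difference in a known direction, and the outcome is one item in a descriptive secondary objective. The primary outcomes and the sample size are untouched.

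**What to change.** Keep the raw count and its reasons. Add to outcome [7] the number of intensifications per patient-year on current treatment, computed as total events divided by total person-time, overall and in 1A/1B and 2A/2B. Give a 95% Poisson interval, or one adjusted for overdispersion if the counts vary more than a Poisson model allows. Take events and person-time over the same current treatment; for combination regimens, do this separately for each drug category so that the denominator is unambiguous.

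The cost is a derived variable, a short definition for combination regimens, and a few table lines. Treatment duration is already listed, so no new data collection is needed, and nothing changes in the primary analysis or the sample size.
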